## Abstract

**Background:**

Effective options for managing insomnia in major depressive disorder (MDD) remain limited. This randomized, single-blind, three-arm parallel trial will compare low-dose laser acupuncture (LA), sham laser acupuncture (SLA), and standard care, evaluating changes in sleep and mood alongside serum biomarkers at three time points (t0 = pre-treatment; t1 = post-treatment, 6 weeks; t2 = follow-up, 12 weeks after treatment).

**Methods:**

A total of 120 inpatients meeting all eligibility criteria will be randomized (1:1:1) to LA, SLA, or control. The primary outcome is the Pittsburgh Sleep Quality Index (PSQI). Secondary outcomes include the Insomnia Severity Index (ISI), the 17-item Hamilton Depression Rating Scale (HAMD-17), serum 5-hydroxytryptamine (5-HT) and cortisol (CORT), and actigraphy. Outcomes are assessed at t0, t1, and t2. Safety will be evaluated by adverse events (AEs) and discontinuations due to adverse effects. Analyses will follow the intention-to-treat principle.

**Discussion:**

By integrating validated clinical endpoints with biomarker assessments, this trial will provide rigorous evidence on the efficacy and safety of low-dose LA for insomnia comorbid with MDD and help clarify potential mechanisms of action. If effective, LA could offer a non-invasive adjunct or alternative to current therapies.

**Registration Details:**

ClinicalTrials.gov, identifier NCT06443242.

## Introduction

Depression and insomnia are highly prevalent and frequently comorbid conditions that significantly contribute to the global disease burden (1–3). Notably, approximately 70% of individuals with depression experience insomnia—a rate three to four times higher than in the general population (1, 4, 5). Their relationship is bidirectional: insomnia exacerbates depressive symptoms, increases the risk of chronicity and relapse, and elevates suicidal ideation (6–8). Shared pathophysiological mechanisms, including dysregulation of the hypothalamic-pituitary-adrenal (HPA) axis leading to aberrant cortisol (CORT) secretion, and alterations in 5-Hydroxytryptamine (5-HT) neurotransmission, underlie this comorbidity and disrupt sleep architecture (9–11). Effectively managing insomnia is therefore critical to improving overall outcomes in patients with major depressive disorder (MDD).

First-line treatments such as cognitive behavioral therapy for insomnia (CBT-I) face limitations in accessibility and cultural acceptability (7, 8), while pharmacotherapies (e.g., hypnotics, antidepressants) often entail undesirable side effects, risk of dependence, and limited long-term efficacy (9, 10). Traditional acupuncture, which modulates neurotransmitters and inflammatory responses, offers benefits for both sleep and mood disorders (12, 13). However, its needle-based nature causes needling pain, bruising, and rarely, serious adverse events (SAEs), which deter some patients and limit its utility (14–17). These limitations highlight the need for effective, non-invasive alternatives.

Laser acupuncture (LA) is a non-invasive modality that applies low-dose laser stimulation to acupoints, combining principles of traditional acupuncture with modern photobiomodulation (18, 19). It is particularly suitable for needle-sensitive populations (e.g., children, the elderly) and has shown promise in improving sleep and mood symptoms by regulating neuroendocrine function and reducing inflammation (20, 21). Photobiomodulation is thought to exert its effects by stimulating mitochondrial cytochrome c oxidase, thereby enhancing cellular energy metabolism and modulating redox signaling (22–24). These changes may regulate neuroendocrine and immune pathways, contributing to the normalization of 5-HT and CORT levels relevant to sleep–wake regulation (25–27). Nevertheless, robust clinical trials investigating LA for depression-related insomnia are scarce, and its effects on underlying biological mechanisms remain poorly elucidated.

Despite its potential, significant evidence gaps exist regarding LA’s efficacy, mechanisms, and applicability in treating insomnia in MDD patients (28, 29). Few high-quality trials have specifically evaluated LA for this comorbidity, and none have comprehensively assessed its impact on sleep quality alongside biomarker changes (29, 30). Furthermore, the mechanisms by which LA may influence objective sleep outcomes and biochemical markers (e.g., 5-HT, CORT) are not yet established (31, 32). This study aims to address these gaps by evaluating the clinical efficacy and safety of LA in improving sleep quality—assessed via the Pittsburgh Sleep Quality Index (PSQI)—and depressive symptoms in MDD patients, and by exploring its potential effects on serum 5-HT and CORT levels. We hypothesize that LA will be superior to sham laser acupuncture (SLA) and standard care in improving sleep quality, reducing depressive symptoms, and modulating biomarker levels, offering a well-tolerated and non-invasive therapeutic option.

In this trial, we will use a controlled study design (LA group vs. SLA group vs. standard care group) to evaluate the clinical efficacy and safety of LA for insomnia in MDD patients; we will dynamically assess subjective sleep quality (via PSQI) and depressive symptoms at baseline, Week 6 (post-treatment), and 12-week follow-up, compare serum CORT and 5-HT changes among the three groups, evaluate LA’s safety via dropout rates related to adverse events (AEs). We also aim to provide evidence for LA’s advantages over SLA and standard care and offer a non-invasive option for eligible patients if effective.

This study is motivated by the urgent need for effective, non-invasive treatments for insomnia in MDD patients. LA represents a promising alternative because of its non-invasiveness, minimal side effects, and potential suitability for home-based application (18, 19). Confirming its efficacy could provide a valuable treatment option for patients who decline needle-based therapies. By incorporating biomarker assessments, this research also seeks to clarify the biological mechanisms underlying LA’s effects, thereby contributing to a more personalized and mechanism-based approach to treatment. Should LA demonstrate clinical benefits, it could help reduce the disease burden associated with comorbid depression and insomnia, improving functional outcomes and quality of life in affected individuals.

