### Withdrawal criteria

Withdrawal criteria are as follows: (1) emergence of suicidal tendencies during the study; (2) occurrence of SAEs; and (3) worsening of insomnia that aggravates depressive symptoms.

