SLA procedures. The sham condition used sham laser applied to the same acupoints as the LA group. Identical probes were secured with medical tape and positioned per the standardized manual, but the device delivered 0 mW output while maintaining the same indicators (lights/sounds) to preserve blinding. Session structure (per-point exposure time, total duration, number of sessions, and treatment sequence) matched the active protocol. Participants and outcome assessors were blinded; operators followed a standardized script. Regarding the validity of sham laser as a control procedure for laser acupuncture studies, in a study which evaluated the use of SLA as a control procedure by comparing verum laser with sham laser reported that treatment with verum laser was indistinguishable from sham laser and there was also no difference in the deqi-like sensations felt by study participants when comparing verum laser with sham laser. Then, the authors also analyzed the pooled findings of three RCTs that compared the use of sham laser with needle acupuncture and found that the credibility of sham laser was not different from that of needle acupuncture (39). Hence, sham laser can serve as valid placebo procedure in laser acupuncture studies.

Control group. Participants in the control arm will continue their stable antidepressant regimen without additional intervention. This group establishes a baseline comparator, enhancing the validity of between-group analyses.

Medication uses across groups. Antidepressant therapy must remain stable for ≥2 weeks before enrolment and throughout the trial. Rescue medication will be limited to oral eszopiclone 0.5 mg, to be taken as needed when insomnia persists for ≥3 consecutive nights. No other sedative–hypnotics (including benzodiazepines) will be permitted unless clinically necessary for safety; any exception requires documentation and approval by the principal investigator. All rescue-medication use will be logged (date, time, dose, indication) and reviewed regularly by the research team. If insomnia worsens alongside depressive symptoms, the participant will be withdrawn and referred for further management.

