### Safety evaluation

Safety will be evaluated throughout the study to ensure participant well-being and to identify potential risks associated with LA, SLA, and control conditions. AEs are defined as any unfavorable or unintended medical occurrence during participation, regardless of its causal relationship to the intervention.

All AEs will be recorded in the CRF, with details on onset, duration, management, and outcome. The investigator will also assess causality, determining whether each AE is related to the intervention. SAEs—such as hospitalization, life-threatening complications, or worsening psychiatric symptoms—will be reported to the ethics committees within 24 hours and followed until resolution or stabilization.

Incidence of AEs will be summarized across groups, and dropout rates due to AEs will be monitored as part of the safety analysis. Participants will receive emergency contact information to report symptoms at any time during the trial. This monitoring framework ensures transparent reporting and timely management of safety concerns.

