### Statistical methods

All analyses will be conducted using statistical package for the social sciences (SPSS) version 28.0 (IBM Corp., Armonk, NY, USA) (51). Continuous variables will be summarized as mean ± standard deviation (SD) for normally distributed data, or as median (interquartile range, IQR) for non-normally distributed data. Categorical variables will be expressed as frequencies and percentages. A two-tailed p value < 0.05 will be considered statistically significant.

Primary outcomes. Changes in PSQI scores, sleep efficiency, total sleep time, and number of awakenings will be analyzed using a mixed-design ANOVA (52), with intervention group (LA, SLA, control) as the between-subject factor and time (baseline, post-treatment, follow-up) as the within-subject factor. Standardized mean differences will be calculated as effect sizes. Significant interactions will be followed by *post-hoc* pairwise comparisons. All primary analyses will follow the intention-to-treat (ITT) principle, with participants analyzed according to initial randomization regardless of adherence or withdrawal.

Secondary outcomes. ISI, HAMD-17, and biomarker levels (CORT, 5-HT) will be analyzed as continuous variables using mixed ANOVA across three time points. Actigraphy-derived sleep parameters will be analyzed similarly. Dropout rates due to AEs will be compared among groups using Pearson’s χ² test or Fisher’s exact test, as appropriate.

A subgroup analysis will be performed in which participants treated with LA will be subdivided into those on selective serotonin reuptake inhibitor (SSRI), serotonin noradrenaline reuptake inhibitor (SNRI) and other antidepressants and on low to moderate dose (less than optimal dose of antidepressant) and on high dose (above the optimal dose of antidepressant) using generalized estimated equation (GEE) where the dependent variable is dummy coded as 0 = without sleep quality disturbance (PSQI ≤ 5) and 1 = with sleep quality disturbance (PSQI > 5).

Sensitivity analysis. A per-protocol analysis will be conducted using the same statistical tests, excluding participants who fail to complete at least 5 of the 6 weekly intervention sessions. Findings will be compared with ITT results.

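### The only tested safety measure, dropout due to adverse events, mixes worsening of depression with harm from the intervention, so an effective laser could mask or reverse a device-related excess in the observed rates

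*Protocol article*

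**What the plan says.** The objectives paragraph of the Introduction says that the trial will "evaluate LA’s safety via dropout rates related to adverse events (AEs"). Statistical methods, under secondary outcomes, gives the matching test: "Dropout rates due to AEs will be compared among groups using Pearson’s χ² test or Fisher’s exact test, as appropriate". No other safety comparison between groups is given a test.

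Three further rules decide what enters that rate.

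- Safety evaluation defines the events broadly: "AEs are defined as any unfavorable or unintended medical occurrence during participation, regardless of its causal relationship to the intervention".
- The same section gives examples of serious adverse events (SAEs): "SAEs—such as hospitalization, life-threatening complications, or worsening psychiatric symptoms".
- Withdrawal criteria list emergent suicidality first and continue: "2) occurrence of SAEs; and (3) worsening of insomnia that aggravates depressive symptoms". The medication paragraph under Interventions repeats the last rule: "If insomnia worsens alongside depressive symptoms, the participant will be withdrawn and referred for further management".

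Other safety reporting is planned. Safety evaluation states "Incidence of AEs will be summarized across groups, and dropout rates due to AEs will be monitored as part of the safety analysis" and has the investigator rate causality. The AE paragraph under Outcomes grades events by severity, provides for incidence by group, and makes only severe events a reason to discontinue treatment. The Abstract names AEs together with discontinuations due to adverse effects, a narrower term than adverse events.

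**The concern.** Read together, these rules put an efficacy-related event inside the safety measure. A participant whose depression worsens has an SAE by the article's own example, meets a withdrawal criterion, and becomes an AE dropout. Depressive symptoms (HAMD-17) are also a secondary efficacy outcome on which LA is expected to beat both comparators. In the control arm, which receives no device, the rate cannot contain device harm at all.

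The measure is also insensitive to what a low-dose device is most likely to cause. Mild and moderate events are observed or managed without a rule that stops treatment, so they enter the test only if the participant leaves because of them.

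At stake is the safety statement. The Introduction hopes to offer a well-tolerated option. A lower or similar AE-dropout rate on LA could be read as support for that when it partly reflects benefit on mood and sleep.

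**Working it through.** **Path through the text**

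1. Depression worsens: an AE regardless of cause, and an SAE by the example in Safety evaluation.
2. An SAE is withdrawal criterion (2).
3. Withdrawal because of an SAE is dropout due to an AE, which is what Statistical methods compares: "Dropout rates due to AEs will be compared among groups using Pearson’s χ² test or Fisher’s exact test".
4. Causality is recorded, but neither the objective nor the test uses it.

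Each step is explicit. It is not stated whether a withdrawal under criterion (1), suicidality, or criterion (3), insomnia that aggravates depression, counts as an AE dropout when no SAE is recorded. The path through criterion (2) does not depend on the answer.

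**Size**

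The article gives no figure for the safety comparison, so there is none to reproduce, and every rate below is an assumption. The arm size of 40 is from the randomisation section.

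- *w*: proportion of controls who worsen and are withdrawn.
- *r*: factor by which LA multiplies that proportion (0.5 = halved, 1 = no benefit).
- *d*: dropout caused by LA itself, taken as independent of worsening.

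Control rate = *w*. LA rate = 1 − (1 − *w·r*)(1 − *d*). The chance that LA shows fewer AE dropouts than control comes from two independent binomials of 40. The last column is the chance that Fisher's exact test of LA against control gives p < 0.05.

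| | w | r | d | LA rate | Control rate | Expected of 40 | P(LA fewer) | Fisher p < 0.05 |
|---|---|---|---|---|---|---|---|---|
| A | 20% | 0.5 | 5% | 1 − 0.90 × 0.95 = 14.5% | 20.0% | 5.8 v 8.0 | 0.69 | 6.1% |
| B | 15% | 0.5 | 5% | 1 − 0.925 × 0.95 = 12.1% | 15.0% | 4.85 v 6.0 | 0.58 | 3.4% |
| C | 10% | 0.5 | 5% | 1 − 0.95 × 0.95 = 9.8% | 10.0% | 3.9 v 4.0 | 0.44 | 1.7% |
| D | 15% | 1 | 5% | 1 − 0.85 × 0.95 = 19.3% | 15.0% | 7.7 v 6.0 | 0.26 | 4.7% |

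In every row, intervention-caused dropout is 5% on LA (40 × 0.05 = 2.0 participants) and 0% on control. In A and B the all-AE rate points the other way. In C the harm is hidden. In D, where LA has no benefit, the rate points the right way. With 36 per arm, the figure in the sample size section, row A gives P(LA fewer) = 0.68 and row D again gives 0.26.

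The Fisher column is for the two-arm table. The planned comparison spans three groups and was not computed.

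**The case against.** The best reply is that safety does not rest on dropout alone. The Abstract, the AE paragraph under Outcomes and Safety evaluation all provide for AEs by group, causality is rated, and an independent committee reviews safety data. Describing AEs without testing them is ordinary practice. This stands: mild and moderate events on LA are outside the test but not outside the report. However, the incidence summary uses the same cause-free definition, so it carries the same mixture, and the Introduction still states the objective as dropout.

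A second reply is that counting AEs regardless of cause is standard, avoids subjective attribution, and keeps worsening depression and suicidality in view as possible harms of treatment. This also stands. It is a reason to keep the all-cause rate and split it, not to replace it. The sham arm does supply a comparator with the same procedure, but LA is hypothesised to be superior to sham as well, so the mixing remains in that contrast.

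A reader might go further in four ways that the documents do not support.

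- That the measure simply captures lack of efficacy: it contains both components.
- That it is uninformative about device harm if LA does not work: row D shows 19.3% against 15.0%, the correct direction.
- That LA would be declared safe on a low rate: no such decision rule appears.
- That hospitalisation as an SAE example contradicts an inpatient population: participants are inpatients at inclusion, but nothing says they stay admitted through follow-up, and a readmission would be a new event.

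**Conclusion.** The concern holds in a limited form. As defined, the one tested safety comparison, which is also the stated safety objective, mixes disease worsening with treatment harm and takes in mild or moderate device-related events only when they lead to dropout. If LA is effective, a true device-related excess can be masked or reversed in the observed rates: 14.5% against 20.0% under scenario A, when the intervention-caused rates are 5% and 0%.

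This rests on assumed rates, on an efficacy effect that the trial hypothesises but has not shown, and on SAE withdrawals being coded as AE dropouts, as the text implies. With 40 per arm the LA-control test would be significant in only about 2% to 6% of trials under these scenarios. The practical risk is therefore misreading of raw rates, or of a non-significant result, more than a false significant finding. The descriptive AE reporting softens the problem but does not remove it.

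**What to change.** 1. Keep all-cause AE dropout for the three arms. Report it with and without withdrawals for disease worsening (depression, insomnia, suicidality), and keep those withdrawals visible as safety events.
2. Add to the Introduction's objective and to Statistical methods a between-group comparison of the proportion of participants with at least one AE, once for all causes and once for intervention-related events. Make LA versus sham the main contrast and give a confidence interval.
3. State whether withdrawals under criteria (1) and (3) alone count as AE dropouts.
4. Reconcile the Abstract (adverse effects), the Introduction, Withdrawal criteria, Safety evaluation and Statistical methods so that one definition runs through all five. This concerns classification and reporting only. No withdrawal or treatment rule needs to change for it.

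The cost is a little more analysis and some wording. AEs and causality are already recorded. Causality ratings bring some subjectivity, which is why the all-cause figures stay beside them. Some withdrawals will have no recorded reason, because Patient recruitment lets participants leave without giving one, so the split table needs a row for unknown reason. The LA safety result may look less favourable than under the present plan.

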## Methods

### Study design

This is a three-year, single-center, randomized, single-blind, three-arm parallel randomized controlled trial (RCT) conducted at The Second Affiliated Hospital, Xinxiang Medical University (XXMU), China. Ethical approval was obtained from the Ethics Committees of XXMU (XYEFYLL-(Research)-2024-36) and Universiti Sains Malaysia (USM) (USM/JEPeM/PP/24070605). The trial is registered at ClinicalTrials.gov (NCT06443242) and follows Consolidated Standards of Reporting Trials (CONSORT) guidelines.

A total of 120 inpatients with major depressive disorder (MDD) and comorbid insomnia will be randomized (1:1:1) to one of three groups: laser acupuncture (LA)—low-dose laser therapy delivered at acupoints; sham laser acupuncture (SLA)—identical procedures without effective laser output; or standard care.

The intervention will last 6 weeks with a 12-week follow-up. The primary outcome is sleeping quality (PSQI), while secondary outcomes include depressive symptoms and serum biomarkers (5-HT, CORT). AEs will be monitored and reported to both ethics committees. **Figure 1** provides a flowchart outlining the study procedures and outcome measures. The CONSORT checklist for this RCT is presented in **Supplementary Material 1**, while the CONSORT flow diagram for participant enrolment, allocation, follow up and analysis is presented in **Supplementary Material 2**.

**Figure 1 f1:**
[figure not shown]
Trial flowchart. LA, laser acupuncture + fixed dose of antidepressant; SLA, sham laser acupuncture + fixed dose of antidepressant; PSQI, Pittsburgh Sleep Quality Index; HAMD-17, 17-item Hamilton Depression Rating Scale; ISI, Insomnia Severity Index; 5-HT, serotonin (5-hydroxytryptamine); AE, adverse events. Each LA and SLA weekly session is characterized by a pre-determined regimen of 5 consecutive days per week, followed by 2 days of rest with 20 minutes per day of laser acupuncture.

### Patient recruitment

All participants in this trial will be recruited from the Department of Psychiatry, The Second Affiliated Hospital of XXMU, China. Recruitment will be carried out through direct approach by the research team as well as announcements posted on hospital information platforms. Interested patients may contact the study staff using the details provided and will undergo an initial eligibility screening. Those who preliminarily meet the inclusion criteria will then be interviewed face-to-face and assessed at baseline by an independent researcher who is blinded to the study objectives. After screening according to the predefined inclusion and exclusion criteria, eligible patients will be informed that they will be randomized to the LA, SLA, or control group. They will also be clearly informed of the possible benefits and risks of participation. Before enrolment, participants will voluntarily sign a written informed consent, and they will be free to withdraw from the study at any time without providing a reason.

